#### The intervention

We active arm is Mg^++^ citrate capsules (150 mg elemental Mg^++^ citrate per capsule), and the control arm is matched placebo capsules. Both will be manufactured by IMIP’s Department of Pharmacology, and will be identical in colour and shape. The 150 mg twice daily dose was chosen with the aim of achieving daily Mg^++^ needs without causing excess of Mg^++^ circulating levels. The study medication packages will be supplied to each local pharmacy with sequential numbers. Code break envelopes will be supplied to the lead pharmacist, but will be not available for the investigative team. Each pack will be individually prescribed for each participant.

Compliance/adherence, adverse events, and clinical intercurrences will be monitored by the research team at each routine prenatal visit until the completion of the treatment. Adherence will be defined as the ingestion of at least 80% of the prescribed dose.

#### Study outcomes

The individual components of the **composite ****
*perinatal *
****outcome** -- preterm birth before 37 weeks gestation, stillbirth after 20 weeks gestation, neonatal death before 28 days after birth, or SGA birthweight under the 3rd percentile – are listed in Table 2. The individual components of the **composite ****
*maternal *
****outcome** -- preeclampsia or eclampsia arising before 37 weeks gestation, severe non-proteinuric hypertension arising before 37 weeks gestation, placental abruption, maternal stroke during pregnancy or ≤ 7 days after delivery, or maternal death during pregnancy or ≤ 7 days after delivery – are listed in Table 2.

**Table 2 T2:** Study outcomes, expected results and key indicators

**Study outcomes**	**Expected result**	**Key indicator**
** *1a. Perinatal composite outcome (Main perinatal outcome)* **	Reduction in the rate of the composite perinatal outcome among infants of women exposed to Mg^++^ vs. placebo	Preterm birth < 37 weeks gestation, stillbirth > 20 weeks gestation, neonatal death < 28 days after birth, or SGA birthweight < 10 percentile
1b. Preterm birth (PTB) (Secondary objective)	Reduction in the rate of PTB among infants of women exposed to Mg^++^ vs. placebo	Birth at gestational age < 37 weeks
1c. Stillbirth (Secondary objective)	Reduction in the rate of stillbirths among pregnant women exposed to Mg^++^	Fetal loss after 20 weeks gestation, in the absence of a major congenital anomaly evident at birth
1d. Small for gestational age birthweight < 10th percentile (Secondary objective)	Reduction in the rate of SGA among infants of women exposed to Mg^++^ vs. placebo	SGA detected by a birthweight < 10th percentile
1e. Neonatal death < 28 days after birth (Secondary objective)	Reduction in the rate of neonatal death SGA among infants of women exposed to Mg^++^ vs. placebo	Neonatal death of a liveborn infant from the date of birth up to and including 27 days after birth, in the absence of a major congenital anomaly evident at birth
1f. Neonatal intensive care unit (NICU) admission (Secondary objective)	Reduction in the rate of NICU admission among infants of women exposed to Mg^++^ vs. placebo	NICU admission < 28 days after birth
** *2a. Maternal composite outcome (Main maternal outcome)* **	Reduction in the rate of the composite maternal outcome among women exposed to Mg^++^ vs. placebo	Preeclampsia or eclampsia < 37 weeks gestation, severe gestational hypertension < 37 weeks gestation, placental abruption in pregnancy, or maternal stroke or death during pregnancy or ≤ 7 days after delivery
2b. Preeclampsia and eclampsia < 37 weeks gestation (Secondary objective)	Reduction in rate of preterm preeclampsia or eclampsia among pregnant women exposed to Mg^++^ vs. placebo	Increased blood pressure > 140/90 mm Hg associated with ≥ 2 proteinuria, and/or seizures, and/or the HELLP Syndrome, arising < 37 weeks gestation
2c. Severe non-proteinuric hypertension < 37 weeks gestation (Secondary objective)	Reduction in rate of preterm severe non-proteinuric hypertension among pregnant women exposed to Mg^++^ vs. placebo	Increased systolic blood pressure > 160 mm Hg or diastolic blood pressure > 105 mm Hg, with ≤ 1+ proteinuria, arising < 37 weeks gestation
2d. Maternal stroke (Secondary objective)	Reduction in rate of maternal stroke among pregnant women exposed to Mg^++^ vs. placebo	Abrupt onset of a focal neurological deficit in the distribution of a brain artery persisting more than 24 hours due to intracerebral hemorrhage or ischemic infarction, arising during pregnancy or ≤ 7 days after delivery
2d. Maternal intensive care unit (ICU) admission (Secondary objective)	Reduction in the rate of maternal ICU admission among women exposed to Mg^++^ vs. placebo	Adult ICU admission during pregnancy or ≤ 7 days after delivery

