**Methods/Design:**

We will complete a multicenter, randomized double-blind clinical trial comparing oral magnesium citrate 150 mg twice daily (n = 2000 women) to matched placebo (n = 1000 women), starting at 12^1/7^ to 20^6/7^ weeks gestation and continued until delivery. We will include women at higher risk for placental dysfunction, based on clinical factors from a prior pregnancy (e.g., prior preterm delivery, stillbirth or preeclampsia) or the current pregnancy (e.g., chronic hypertension, pre-pregnancy diabetes mellitus, maternal age > 35 years or pre-pregnancy maternal body mass index > 30 kg/m^2^). The primary perinatal outcome is a composite of preterm birth < 37 weeks gestation, stillbirth > 20 weeks gestation, neonatal death < 28 days, or SGA birthweight < 3rd percentile. The primary composite maternal outcome is preeclampsia arising < 37 weeks gestation, severe non-proteinuric hypertension arising < 37 weeks gestation, placental abruption, maternal stroke during pregnancy or ≤ 7 days after delivery, or maternal death during pregnancy or ≤ 7 days after delivery.

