## Methods/Design

### Study objectives and design

#### Primary objectives

i. In women with 1 or more risk factors for an adverse pregnancy outcome, to determine whether there is a reduction in the **composite ****
*perinatal *
****outcome** -- preterm birth before 37 weeks gestation, stillbirth after 20 weeks gestation, neonatal death before 28 days after birth, or SGA birthweight under the 3rd percentile -- following the administration of oral Mg^++^ citrate 150 mg twice daily versus oral placebo twice daily.

ii. In women with 1 or more risk factors for an adverse pregnancy outcome, to determine whether there is a reduction in the **composite ****
*maternal *
****outcome** -- preeclampsia or eclampsia arising before 37 weeks gestation, severe non-proteinuric hypertension arising before 37 weeks gestation, placental abruption, maternal stroke during pregnancy or ≤ 7 days after delivery, or maternal death during pregnancy or ≤ 7 days after delivery -- following the administration of oral Mg^++^ citrate 150 mg twice daily versus oral placebo twice daily.

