#### Secondary objectives

i. In women with 1 or more risk factors for an adverse pregnancy outcome, to determine whether there is a reduction in any single component of the **composite ****
*perinatal *
****outcome** -- preterm birth before 37 weeks gestation, stillbirth after 20 weeks gestation, neonatal death before 28 days after birth, or SGA birthweight under the 3rd percentile -- following the administration of oral Mg^++^ citrate 150 mg twice daily versus oral placebo twice daily.

ii. In women with 1 or more risk factors for an adverse pregnancy outcome, to determine whether there is a reduction in any single component of the **composite ****
*maternal *
****outcome** -- preeclampsia or eclampsia arising before 37 weeks gestation, severe non-proteinuric hypertension arising before 37 weeks gestation, placental abruption, maternal stroke during pregnancy or ≤ 7 days after delivery, or maternal death during pregnancy or ≤ 7 days after delivery -- following the administration of oral Mg^++^ citrate 150 mg twice daily versus oral placebo twice daily.

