#### Data analysis and sample size

All outcomes will be analyzed by intention to treat (ITT), using logistic regression analysis. The main effects sizes for each outcome will be expressed as a rate (95% CI) and odds ratio (95% CI).

At the time of study entry, on the day of randomization, all women will undergo a measured serum Mg^++^ and creatine concentration. Any woman whose serum Mg^++^ concentration is over 9.5 mmol/dL, or whose estimated glomerular filtration rate (eGFR is under 60 mL/min/1.73 m^2^, will be excluded from the trial, and will not be counted in the ITT analysis. Otherwise, all other randomized participants will be included in the ITT analysis regardless of whether they complete the trial.

An efficacy analysis (on-treatment) analysis will be done for each study outcome, wherein women who were adherent with at least 80% of their dispensed tablets will be analyzed.

At a sample size of 1000 women assigned to placebo and 2000 women assigned to Mg^++^ citrate, with power of 80% and a 2-sided P-value of 0.05, we will be able to detect at least a 22% relative risk reduction in the primary perinatal composite outcome, assuming a primary perinatal composite outcome rate of 18% in the placebo group and 14% in the Mg^++^ group. In Recife there are 25,000 births a year. Of these 25,000, at least 30% (7,500) would attend one of the study prenatal clinics, & of those 7,500, 60% (4,500) would meet ≥1 of the eligibility criteria. With a participation rate of 50%, 2,250 women can be recruited in a year, thus requiring 1.25 years to recruit all women, and 2 years ascertain all primary outcome events.

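### The primary perinatal composite is defined with two different SGA cut-offs (< 3rd and < 10th percentile), and the 18% vs 14% planning rates are not tied to either

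*Protocol article*

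**What the plan says.** All places are in the protocol article.

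- **Abstract, Methods/Design:** the primary perinatal composite ends with "neonatal death < 28 days, or SGA birthweight < 3rd percentile".
- **Primary objective i:** "stillbirth after 20 weeks gestation, neonatal death before 28 days after birth, or SGA birthweight under the 3rd percentile".
- **Secondary objective i** (single components of the composite): "neonatal death before 28 days after birth, or SGA birthweight under the 3rd percentile".
- **Study outcomes, text above Table 2:** the components, including "SGA birthweight under the 3rd percentile – are listed in Table 2".
- **Table 2, row 1a** (labelled as the main perinatal outcome): "neonatal death < 28 days after birth, or SGA birthweight < 10 percentile".
- **Table 2, row 1d** (SGA as a secondary outcome): "SGA detected by a birthweight < 10th percentile".
- **Data analysis and sample size:** 1000 placebo and 2000 magnesium women, 80% power, two-sided 0.05, "assuming a primary perinatal composite outcome rate of 18% in the placebo group and 14% in the Mg^++^ group". No cut-off and no source is given for the 18%.

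Row 1c defines stillbirth as "Fetal loss after 20 weeks gestation, in the absence of a major congenital anomaly evident at birth". Row 1e has a similar exclusion for neonatal death. Row 1a and the objectives do not mention it.

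**The concern.** The two versions are different endpoints. A composite with SGA < 10th percentile counts more and milder cases than one with SGA < 3rd. They differ in event rate, in clinical meaning and, for a given relative effect, in power.

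The sentence above Table 2 refers the reader to the table for the components, and the table then gives a different cut-off. An analyst working from the text and one working from the table would analyse different primary outcomes, and each could cite the protocol. The 18% vs 14% rates were presumably derived for one version, and the reader cannot tell which. If the choice were left until outcome data by arm had been seen, the primary result would be open to the charge of selection.

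**Working it through.** **1. The statements side by side**

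| Place | SGA cut-off |
|---|---|
| Abstract (composite) | < 3rd |
| Primary objective i (composite) | < 3rd |
| Secondary objective i (composite and its single components) | < 3rd |
| Study outcomes text (composite) | < 3rd |
| Table 2 row 1a (composite) | < 10th |
| Table 2 row 1d (single component) | < 10th |

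Four of the five statements of the composite say < 3rd. The prose is consistent with itself, and so is Table 2.

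**2. The plan's own power**

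Inputs from Data analysis and sample size: p1 = 0.18 (n1 = 1000), p2 = 0.14 (n2 = 2000), two-sided 0.05. The method is the pooled-variance normal approximation.

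- Pooled rate = (1000 × 0.18 + 2000 × 0.14) / 3000 = 0.1533
- SE under the null = √[0.1533 × 0.8467 × (1/1000 + 1/2000)] = 0.01395
- SE under the alternative = √[0.18 × 0.82/1000 + 0.14 × 0.86/2000] = 0.01442
- z = (0.04 − 1.96 × 0.01395) / 0.01442 = 0.877, so power = 0.81

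The stated 80% is reproduced; 80% power needs 975 placebo women. The relative reduction is 1 − 14/18 = 22.2%, as stated.

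**3. Direction of the difference**

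Any birthweight under the 3rd percentile is also under the 10th. The < 3rd composite is therefore a subset of the < 10th composite, and its rate cannot be higher. At a fixed relative reduction and sample size, a lower rate means lower power.

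**4. Size, as an illustration**

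The documents give no composite rate for either version. The table holds n = 1000/2000 and the relative reduction at 22.2%, and varies an assumed placebo rate.

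| Assumed placebo rate | Power | Placebo women for 80% power |
|---|---|---|
| 13% | 0.66 | 1420 |
| 14% | 0.69 | 1305 |
| 15% | 0.72 | 1206 |
| 16% | 0.76 | 1119 |
| 17% | 0.78 | 1043 |
| 18% | 0.81 | 975 |
| 20% | 0.86 | 859 |
| 22% | 0.89 | 764 |

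**5. Does the 18% reveal its version?**

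Table 1 gives pooled control rates of 10.5% for preterm birth and 11.9% for SGA < 10th. Leaving deaths aside:

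- < 10th, components independent: 1 − 0.895 × 0.881 = 21.2%; no overlap: 10.5 + 11.9 = 22.4%.
- < 10th, with 23% of preterm infants SGA (European figure in the Background): 10.5 + 11.9 − 0.23 × 10.5 = 20.0%.
- < 3rd, with an assumed 3% to 6% of infants under the 3rd percentile: 13.2% to 15.9% if independent, 13.5% to 16.5% with no overlap.

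The planned 18% lies between these ranges, so it does not identify the cut-off.

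**The case against.** **The 3rd percentile may simply be intended, with row 1a a slip.** The count and the primary objective support this. But row 1d repeats the 10th percentile in both its label and its indicator, so a single mistyped cell is not shown. The document alone cannot settle the intention.

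**A later analysis plan may fix the definition.** It may. It would then have to contradict part of this protocol, so the contradiction still needs correcting here.

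**A reader might infer that the trial is underpowered under < 3rd. The documents do not support that.** The rates in step 5 come from pooled earlier trials and a European study, whereas this trial enrols women with at least one risk factor. If the preterm rate were 15% to 16% (an assumption), with 3% to 5% of infants under the 3rd percentile, 10% to 11.9% under the 10th and the 23% overlap, the < 3rd composite would be preterm + SGA3 × (1 − 0.23 × preterm / SGA10). That is about 17.0% to 19.5%, with power of about 0.78 to 0.84. Deaths not already counted as preterm or SGA would raise both versions further.

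**A reader might infer an inflated type I error.** Testing both versions and keeping the better would raise the two-sided error to about 7% to 8%, under assumed correlations of 0.77 to 0.89 between the two test statistics. Nothing in the document plans this, so it is a risk of leaving the choice open and not a property of the design.

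**A reader might infer that rows 1c and 1e make the composite differ from the union of its components.** That depends on reading those rows as separate outcomes. They can equally be read as the working definitions of the components named in row 1a, in which case the anomaly exclusion carries over. This is at most a clarification.

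**Conclusion.** The point stands as an internal contradiction in a primary endpoint: four statements of the composite use SGA < 3rd percentile, Table 2 row 1a uses < 10th, and no rule says which governs. Row 1d conflicts with secondary objective i in the same way.

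The sample-size calculation is not in error: 18% vs 14% is fixed as a pair of numbers and gives the stated power. What is missing is the definition that it belongs to. That < 3rd has the lower rate and, at equal relative effect, the lower power follows from the definitions. The size of the gap does not: it depends on the assumed placebo rates and on a relative reduction of 22% for both versions. Because this is a main outcome of the trial, it must be settled, although the repair is small.

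**What to change.** Before any unblinded look:

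1. Amend the documents so that the abstract, both objectives, the Study outcomes text and Table 2 row 1a carry one SGA cut-off. The stated primary objective and the majority of the statements favour < 3rd. In that case, correct row 1a, add the < 3rd component as the secondary outcome that secondary objective i names, and keep SGA < 10th only as a separately named secondary outcome. If the sponsor can document that < 10th was intended, correcting the text instead also resolves the contradiction.
2. State which definition the 18% and 14% refer to. If they were derived for the version not chosen, restate the rates and the power.
3. As a minor clarification, say whether the congenital-anomaly exclusion in rows 1c and 1e also applies within the composite.

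The cost is a text amendment and possibly a less favourable stated power. No new data are needed.

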#### Randomization scheme

Participants will be randomized in a 2:1 fashion to either Mg^++^ citrate or placebo. Block randomization will be used to ensure a balanced number of participants in each group at any time during the study.

#### Data analysis and sample size

All outcomes will be analyzed by intention to treat (ITT), using logistic regression analysis. The main effects sizes for each outcome will be expressed as a rate (95% CI) and odds ratio (95% CI).

At the time of study entry, on the day of randomization, all women will undergo a measured serum Mg^++^ and creatine concentration. Any woman whose serum Mg^++^ concentration is over 9.5 mmol/dL, or whose estimated glomerular filtration rate (eGFR is under 60 mL/min/1.73 m^2^, will be excluded from the trial, and will not be counted in the ITT analysis. Otherwise, all other randomized participants will be included in the ITT analysis regardless of whether they complete the trial.

An efficacy analysis (on-treatment) analysis will be done for each study outcome, wherein women who were adherent with at least 80% of their dispensed tablets will be analyzed.

At a sample size of 1000 women assigned to placebo and 2000 women assigned to Mg^++^ citrate, with power of 80% and a 2-sided P-value of 0.05, we will be able to detect at least a 22% relative risk reduction in the primary perinatal composite outcome, assuming a primary perinatal composite outcome rate of 18% in the placebo group and 14% in the Mg^++^ group. In Recife there are 25,000 births a year. Of these 25,000, at least 30% (7,500) would attend one of the study prenatal clinics, & of those 7,500, 60% (4,500) would meet ≥1 of the eligibility criteria. With a participation rate of 50%, 2,250 women can be recruited in a year, thus requiring 1.25 years to recruit all women, and 2 years ascertain all primary outcome events.

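### The 80% adherence rule has two different denominators, and the one used for the on-treatment analysis can drop women because they delivered early

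*Protocol article*

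**What the plan says.** Under The intervention, the protocol article states: "Adherence will be defined as the ingestion of at least 80% of the prescribed dose". Under Data analysis and sample size, the on-treatment set is restricted differently: "women who were adherent with at least 80% of their dispensed tablets will be analyzed". The product is a capsule in the first place ("the control arm is matched placebo capsules") and a tablet in the second.

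Three further statements give the denominator its weight:
- The abstract has treatment started in the second trimester and "weeks gestation and continued until delivery", so the length of exposure depends on when the woman delivers.
- The restricted analysis is broad in scope: "An efficacy analysis (on-treatment) analysis will be done for each study outcome". That includes preterm birth before 37 weeks, alone and within the perinatal composite.
- The main analysis is separate: "All outcomes will be analyzed by intention to treat (ITT), using logistic regression analysis".

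On supply, the article says "Each pack will be individually prescribed for each participant". Adherence "will be monitored by the research team at each routine prenatal visit until the completion of the treatment". It gives no pack size, refill interval or rule for capsules still unused at delivery.

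**The concern.** One threshold is applied to two quantities that need not be equal. If the denominator is what was handed out, a woman who took every capsule due can still fall below 80% because delivery left part of her last pack unused. The same leftover is a larger share of a short course than of a long one. Entry to the analysed set then depends partly on gestational age at delivery, which is itself part of the primary perinatal outcome.

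At stake is an analysis named as one of efficacy and planned for every outcome. It could lose outcome events because of how capsules are counted. If the loss differed between arms, its odds ratio would not measure the effect of magnesium.

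**Working it through.** **The plan's own figure.** Inputs from Data analysis and sample size: 1000 placebo, 2000 magnesium, 18% versus 14%, two-sided 0.05.
- Pooled rate = (180 + 280)/3000 = 0.1533. Null standard error = √(0.1533 × 0.8467 × (1/1000 + 1/2000)) = 0.01396.
- Alternative standard error = √(0.18 × 0.82/1000 + 0.14 × 0.86/2000) = 0.01442.
- z = (0.04 − 1.96 × 0.01396)/0.01442 = 0.88, so power is 81%. The stated 80% is reproduced, and the sample size is not in dispute.

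**A woman who takes a fraction *a* of her doses, one supply to 40 weeks (assumed).** With start at week S, she falls below 80% of dispensed if she delivers before S + 0.8 × (40 − S)/*a*.
- *a* = 1: 34.4 weeks (S = 12 1/7), 35.2 (S = 16), 36.2 (S = 20 6/7).
- *a* = 0.9: 36.9, 37.3 and 37.9 weeks.

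**Refills every *m* weeks (assumed), no dose missed, delivery just after a refill.** Worst-case ratio = F/(F + *m*), where F is the whole refill periods completed, in weeks.
- *m* = 4, S = 16: 12/16 = 0.75 at 28–30 weeks, 16/20 = 0.80 at 32–34, 20/24 = 0.83 at 36–39.
- *m* = 2, S = 16: 10/12 = 0.83 at 26 weeks, 22/24 = 0.92 at 39, so she never fails.
- *m* = 2, S = 20 6/7: 4/6 = 0.67 at 26 weeks, 6/8 = 0.75 at 28, 8/10 = 0.80 at 30. A late starter can fail even with short packs.

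**Imperfect intake, by simulation.** Assumptions: entry uniform over the eligible weeks; 13.6% preterm (the national rate in the Background, not a trial figure); preterm births at 24–37 weeks, either spread evenly or skewed late; intake averaging 92% (SD 8%) in everyone, so that 93% of preterm and of term deliverers take at least 80% of capsules due. A woman is kept if *a* × days ÷ (pack length × number of packs opened) is at least 0.80.

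| Supply | Preterm kept | Term kept | Preterm rate in analysed set |
|---|---|---|---|
| 7-day packs (late-skewed only) | about 88% | about 90% | not tabulated |
| 14-day packs | 75–81% | 84–85% | 12.1–13.0% |
| 28-day packs | 49–62% | 70–71% | about 10–12% |
| 56-day packs | 26–34% | 40% | 9.5–11.7% |
| One supply to 40 weeks | 5–12% | 82% | 0.9–2.2% |

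The direction is the same in every scheme tested. The size is not.

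**Equal loss in both arms.** Suppose 50% of women with an event and 80% without are kept in each arm.
- Placebo: 0.09/(0.09 + 0.656) = 12.1% of 746 women. Magnesium: 0.07/(0.07 + 0.688) = 9.2% of 1516 women.
- The odds in each arm are multiplied by 0.5/0.8, so the placebo-to-magnesium odds ratio stays at (0.18/0.82)/(0.14/0.86) = 1.35.
- Power falls from 81% to about 55%.

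**Unequal loss, no true effect (18% in both arms).** Keep 80% of non-events in both arms, 50% of placebo events and 40% of magnesium events. The rates are 0.09/0.746 = 12.1% and 0.072/0.728 = 9.9%, a spurious relative risk of 0.82. These retention figures are illustrative. Nothing in the article gives them.

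**The case against.** The strongest reply is that the conflict may be verbal only. Packs are individually prescribed, so prescribed and dispensed could be the same quantity, and how leftovers are counted is commonly settled in a full protocol. A prescribed dose read as a full course to term would also carry the early-delivery problem. This stands in part: the article does not show that one of its two denominators is sound and the other biased. But it does print two rules that can give different sets, and neither says that the count stops at delivery.

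A reader might infer that the adherent-only analysis would produce a benefit where none exists. The documents do not support that. Early-delivery loss acting equally in both arms cannot move the odds ratio, which is the protocol's effect measure.

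A spurious reduction close to the 22% target can be constructed. With 18% true risk in both arms and 30% of the magnesium arm non-adherent at 24–27% risk, magnesium adherers show (0.18 − 0.30 × 0.24)/0.70 = 15.4%, or 14.1% at the higher risk. Against 18% that is a reduction of 14–21%. But this compares adherers with an unselected placebo arm, while the restriction as worded covers both arms. With 20% placebo non-adherence at the same risks, placebo adherers show 16.5% or 15.75%, and the reduction is 6–10%. With 30% it is zero.

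Intolerance of magnesium is a possible source of unequal adherence, but the article's section on the proposed intervention says that a laxative effect is rarely detectable, and the trial is double-blind.

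**Conclusion.** The two denominators must be reconciled. Under the literal dispensed rule, women who deliver early tend to be dropped more often. The excess loss is a few percentage points with 7- to 14-day packs (about 10 for 14-day packs if preterm births are spread evenly over 24–37 weeks). It reaches nearly all preterm births with one supply to term. All these sizes rest on assumed pack sizes, intake and delivery timing, and on leftovers being counted as missed.

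The certain cost, if such loss occurs, is events and power in this analysis. Bias in the treatment comparison needs retention that differs by arm. That is possible because adherence arises after randomisation, but it is not documented. Intention to treat on all outcomes protects the main conclusion, so this is a worthwhile correction to a secondary analysis and not a threat to the trial's primary result.

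**What to change.** - Use one definition in both sections: capsules taken divided by capsules due from randomisation to delivery, or to the end of treatment if earlier. A woman who misses no dose then scores 100% whenever she delivers. Say capsules in both places.
- Label the adherent-only analysis supportive to the intention-to-treat analysis and drop the efficacy label. Restricting to adherers remains a selection after randomisation under any denominator.
- Optionally, add a complier-average estimate that keeps all randomised women, as a sensitivity analysis. It has a wider interval and assumes that women below the 80% cut-off gain nothing, so it is no necessary replacement.

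The first two changes are wording. They need capsule counts and the delivery date for each woman. Adherence monitoring is already planned at each prenatal visit, though the article does not say that it is by capsule count. The optional estimate costs one further model.

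### Two primary composites are declared without ranking, but the trial is sized on the perinatal one alone at the full two-sided 0.05, with no rule linking them and no detectable maternal effect

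*Protocol article*

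**What the plan says.** The abstract (Methods/Design) gives both composites the same status. On one side, "The primary perinatal outcome is a composite of preterm birth < 37 weeks gestation", with further components. On the other, "The primary composite maternal outcome is preeclampsia arising < 37 weeks gestation", again with further components. The section Primary objectives lists the perinatal composite as (i) and the maternal composite as (ii), with no ranking in the text. Table 2 labels each as a main outcome, in rows 1a and 2a. Study design calls the trial a superiority trial.

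The section Data analysis and sample size contains the only error rate and the only power in the article, and both belong to the perinatal composite: "with power of 80% and a 2-sided P-value of 0.05, we will be able to detect at least a 22% relative risk reduction", "assuming a primary perinatal composite outcome rate of 18% in the placebo group and 14% in the" magnesium group. The same section says that all outcomes will be analysed by logistic regression, with rates and odds ratios each given a 95% confidence interval.

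No event rate, detectable effect or power is given for the maternal composite. Nothing says whether the trial succeeds on one composite or only on both, in what order they are tested, or how the 0.05 is shared.

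**The concern.** Two unranked primaries, each judged at two-sided 0.05, give the trial two chances of a false positive primary. Suppose the perinatal result is null and the maternal P-value falls just under 0.05. Nothing in the article would stop that from being reported as a positive primary result, and a reader could not tell what error rate lay behind it.

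The reverse risk matters too. With no detectable maternal effect on record, a non-significant maternal result cannot be judged: it could reflect no benefit or too few events.

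The sample size makes this more than a reporting detail. The 3,000 women deliver the stated power only if the perinatal composite keeps the whole 0.05. A later equal split would not deliver it, and nor would a requirement that both composites succeed.

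**Working it through.** **Inputs.** From Data analysis and sample size: 1000 placebo and 2000 magnesium; 18% and 14% for the perinatal composite; two-sided 0.05; 80% power. The 2:1 ratio agrees with Randomization scheme. Correlations between the two test statistics, and placebo rates for the maternal composite, are assumptions; the article gives neither.

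**1. The plan's own power figure.** Power = Φ[(p₁ − p₂ − z·SE₀)/SE₁], with SE₀ from the pooled rate and SE₁ from the separate rates.
- Pooled rate = (1000 × 0.18 + 2000 × 0.14)/3000 = 0.1533
- SE₀ = √[0.1533 × 0.8467 × (1/1000 + 1/2000)] = 0.01395
- SE₁ = √[0.18 × 0.82/1000 + 0.14 × 0.86/2000] = 0.01442
- At 0.05: (0.04 − 1.960 × 0.01395)/0.01442 ≈ 0.88, so power is 81.0%

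Taking exactly a 22% reduction (14.04%) gives 80.2%. Other standard formulas for 18% against 14% give 79.2% (unpooled), 79.5% (continuity-corrected) and 81.6% (log odds ratio). The stated 80% is reproduced.

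**2. Error across two primaries, each at two-sided 0.05, if either may be claimed.**
- Independent tests: 1 − 0.95² = 9.75%
- False benefit only, independent tests: 1 − 0.975² = 4.9%

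The correlated cases come from a bivariate normal calculation.

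| Correlation of tests | At least one false significant result | At least one false claim of benefit |
|---|---|---|
| 0 | 9.75% | 4.9% |
| 0.5 | 9.07% | 4.5% |
| 0.7 | 8.35% | 4.2% |
| One test only | 5% | 2.5% |

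**3. Perinatal power after an equal split (0.025 each).** (0.04 − 2.241 × 0.01395)/0.01442 ≈ 0.61, so power is 72.7%. The relative reduction detectable with 80% power moves from 22.0% to 24.0%. Keeping 80% for 18% against 14% would need 1178 + 2356 = 3534 women.

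**4. Maternal composite with 1000/2000 at two-sided 0.05, same formula, assumed placebo rates.**

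| Assumed placebo rate | Relative reduction detectable with 80% power | Power for a 22% reduction |
|---|---|---|
| 6% | 38% | 35% |
| 8% | 33% | 44% |
| 10% | 30% | 53% |

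Over a wider range, power for a 22% reduction is 30% at a rate of 5% and 72% at 15%.

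**The case against.** The strongest reply is that a testing order for two primaries usually belongs in the SAP. The SAP is not shown, and a journal article condenses the full protocol. The sample-size sentence is also not wrong: a fixed-sequence plan with the perinatal composite first would contain that very sentence. The loss of power to 73% arises only under an equal split, which the article does not propose. This stands to the extent that the absence of a rule alone would not be a finding. What remains is what the article itself fixes: two unranked primaries with a sample size and power that hold for only one of them, and only under some of the rules a SAP might later adopt.

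A reader might go further and infer that the trial is set up to claim success on either composite, with a false-claim rate of nearly 10%. The article does not support that.
- It states no success rule. Testing the maternal composite at 0.05 is inferred from the 95% intervals, which are a reporting format. If both composites had to succeed, there would be no inflation, but joint power could not exceed the lower of the two powers.
- The 9.75% needs independent tests. The article's rationale is that placental dysfunction drives hypertensive disease, poor growth and indicated preterm delivery together, so positive correlation is likely.
- The figure is two-sided and counts false findings of harm. For false benefit the ceiling is 4.9%.

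A reader might also infer that the maternal comparison is shown to be underpowered. It is not: every maternal figure depends on an assumed event rate.

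Finally, whether distinct maternal and perinatal questions need joint error control, and which comes first, is partly a design choice. That is a reason to state the choice.

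**Conclusion.** The point holds in a conditional form. The article treats two composites as primary, sizes the trial on one of them at the full two-sided 0.05, and leaves the error rate across the pair uncontrolled as written. If either composite may carry a positive claim, the chance of at least one false significant primary is about 8.3% to 9.75% for correlations from 0.7 down to 0. For false claims of benefit it is about 4.2% to 4.9%, against 2.5%.

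The stated 80% power is correct for the perinatal composite tested alone at 0.05, and drops to about 73% under an equal split. That the maternal composite has no stated detectable effect is true under any success rule; how large that effect is cannot be settled from the article. This should be corrected, but it does not invalidate the design.

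**What to change.** Pre-specify a fixed sequence in the protocol and SAP. Test the perinatal composite at two-sided 0.05. Treat the maternal composite as confirmatory at two-sided 0.05 only if the first test is significant; otherwise report its estimate and confidence interval without a confirmatory claim.

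Beside the perinatal figure, state the maternal effect detectable with 1000 and 2000 women and the placebo rate assumed for it. The illustrative values above (38%, 33% or 30% at 6%, 8% or 10%) show the form; the sponsor should supply and justify the rate.

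The cost is two sentences on the sequence and one line on the detectable effect. The sample size and the stated perinatal power do not change. The price is that a maternal benefit cannot be claimed as confirmed if the perinatal result is not significant. If the sponsor wants a stand-alone maternal claim, alpha has to be divided and the sample size or stated power revised to match.
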